### Patients of cataract surgery for both eyes

We include participants undergoing cataract surgery for single and both eyes. The surgery for both eyes among the intervention group will be completed within the same time-scale, one to two weeks, and the same kind of IOLs will be used for both eyes. Outcomes will be measured at three months after the latest surgery.

### Primary outcome

We will assess depressive symptoms as a primary outcome of the present study using the short version geriatric depression scale GDS-15. Prevalence of depression, median of GDS-15, and the mean value of difference between baseline and three months later will be compared between the intervention group and the control group.

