### Self-reported questionnaires

Depressive symptoms are measured using GDS-15; a self-administered questionnaire consisting of 15 items
[43]. The sensitivity and specificity of GDS-15 compared with diagnosis according to the Diagnostic and Statistical Manual of Mental Disorders (fourth edition) was 92.7% and 54.8% with a cut-off point of four out of five, and 84.8% and 67.7% with a cut-off point of six out of seven, respectively
[44]. According to a meta-analysis about the validity of GDS-15, the mean sensitivity was 0.805 and the mean specificity was 0.750, respectively
[45]. A higher score on the GDS-15 was significantly associated with self-report and clinician-administered measures of suicidal ideation
[46] and higher rates of suicide
[47]. Subjective sleep quality and daytime sleepiness are assessed using the Pittsburgh Sleep Quality Index (PSQI)
[48] and the Epworth Sleepiness Scale (ESS)
[49, 50], respectively. Chronotype and subjective visual function are determined by the ‘morningness-eveningness’ questionnaire (MEQ)
[51], the Munich Chronotype Questionnaire (MCTQ)
[52], and the National Eye Institute Visual Function Questionnaire (NEI VFQ25)
[53, 54].

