### Sample size

According to the HEIJO-KYO study
[26], a community-based cohort study among the elderly (mean age ± standard deviation: 72 ± 7.1) in the same district as the present study, the prevalence of depression was 20.0% (101 out of 506)
[37]. To detect its 7% difference as significant at a two-sided α level of 5% with a power of 80%, it was calculated that 475 participants in each group would be required. Assuming a dropout of 5%, we estimated that a total of 1,000 participants would be needed.

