### Statistical analysis

We will compare the outcomes between the control group and the intervention group based on the intention-to-treat principle. For missing values due to loss to follow-up after baseline measurement, we will impute baseline data using the last observation carried forward (LOCF) method. For continuous variables with normal distributions, the mean and standard deviation will be reported. For variables not distributed normally, the median and interquartile range will be reported. Means, medians, and proportions will be compared using the t test, the Mann-Whitney U test, and the χ^2^ test, respectively. We will use analysis of covariance to estimate adjusted mean values and 95% CIs. The prevalence of the two groups will be tested using multivariate logistic regression analysis. To assess the phase, amplitude, and robustness of the circadian rhythm, we will use the cosinor model
[69], the sigmoidally transformed cosine model
[70], and the generalised additive model
[71]. We will conduct a subgroup analysis at baseline according to the severity of cataract and chronotype.

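### The primary outcome lists three GDS-15 comparisons with no lead comparison and no adopted depression cut-off, so the 5% level does not protect the primary conclusion if any one may be claimed

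*Protocol article*

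**What the plan says.** In the protocol article, the Primary outcome section states: "We will assess depressive symptoms as a primary outcome of the present study", measured by the GDS-15. It continues: "Prevalence of depression, median of GDS-15, and the mean value of difference between baseline and three months later will be compared" between the two groups. The three comparisons carry no order, and no rule says what follows if they disagree.

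The Statistical analysis section gives each type of measure its own test: "Means, medians, and proportions will be compared using the t test, the Mann-Whitney U test" and, for proportions, the chi-square test. It adds analysis of covariance to estimate adjusted means with confidence intervals, and says "The prevalence of the two groups will be tested using multivariate logistic regression analysis". No multiplicity rule appears.

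A 5% significance level appears only under Sample size. There the reference prevalence of depression is 20.0% (101 of 506) from a community cohort, and the aim is "To detect its 7% difference as significant at a two-sided α level of 5% with a power of 80" per cent. This gives 475 per group, and 1,000 in total after 5% dropout. The GDS-15 cut-off behind the 20.0% is not given.

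Self-reported questionnaires reports sensitivity and specificity of 92.7% and 54.8% "with a cut-off point of four out of five", and of 84.8% and 67.7% "with a cut-off point of six out of seven". Neither is adopted as the trial's definition of depression.

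**The concern.** A trial sized for one test at 5% should have one comparison that decides it, or a rule for combining several. Here three stand side by side under the primary heading, and the one that sized the trial cannot be computed from the article because its threshold is not fixed.

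Two things are at stake. First, if a significant result on any of the three may be reported as the primary finding, the error rate of that finding is not 5%. Second, the three can disagree: prevalence looks at one threshold, the median ignores baseline, and mean change uses baseline. The text gives no way to say what the trial then concludes.

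**Working it through.** **Inputs.** From Sample size: 20.0% prevalence, 7-point difference, two-sided 5%, 80% power, 475 per group, 5% dropout. From Primary outcome and Statistical analysis: three comparisons with three tests. From Self-reported questionnaires: cut-offs 4/5 (score of 5 or more) and 6/7 (score of 7 or more). Assumed, because the article gives no mean, SD or correlation for the GDS-15: the score distribution in step 3.

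**Step 1. Reproduce the stated sample size.** Take 20% against 13%, pooled-variance formula:

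n = [1.960 × √(2 × 0.165 × 0.835) + 0.842 × √(0.20 × 0.80 + 0.13 × 0.87)]² / 0.07² = (1.029 + 0.440)² / 0.0049, which gives 441 per group.

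The continuity correction, (n/4) × [1 + √(1 + 4/(0.07n))]², gives 469. The stated 475 is within 3% of this. Reading the difference as 20% against 27% gives 575 (603 with correction), which does not match. Dropout: 475 / 0.95 = 500 per group, 1,000 in total. The figure therefore reproduces as a single prevalence test at two-sided 5%.

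**Step 2. Error rate under independence.** With three tests at 5%, the chance of at least one false positive is 1 − 0.95³ = 14.3%. The tests share data, so the true figure is lower.

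**Step 3. Error rate allowing for correlation.** Simulation under no effect: 475 per group, 4,000 trials per setting, beta-binomial scores from 0 to 15 (the two beta parameters summing to 4), baseline and follow-up linked by a latent normal correlation. Tests: chi-square on follow-up prevalence, Mann-Whitney on follow-up score, t test on change.

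| Mean score | Latent correlation | Any of three, cut-off 4/5 | Any of three, cut-off 6/7 | Any, either cut-off allowed | Prevalence only, either cut-off |
|---|---|---|---|---|---|
| 3 | 0.30 | 11.3% | 12.2% | 14.1% | 8.4% |
| 3 | 0.50 | 11.8% | 12.7% | 15.0% | 8.8% |
| 3 | 0.70 | 11.9% | 12.6% | 14.8% | 8.6% |
| 3 | 0.85 | 12.4% | 13.2% | 15.4% | 8.8% |
| 4 | 0.70 | 12.5% | 13.2% | 15.1% | 8.7% |

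Each test alone rejected in 4.6% to 5.6% of trials. The simulation error near 12% is √(0.12 × 0.88 / 4,000), about 0.5 percentage points. Further runs (means 2.7 to 4, correlation 0.5 or 0.7, 3,000 trials each) gave 10.7% to 13.0% for the three tests, 13.1% to 15.6% with the cut-off open, and 8.3% to 9.4% for prevalence alone with the cut-off open. A continuity-corrected chi-square gave 11.3% to 11.5% for the three tests.

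Allowing both cut-offs makes four tests, for which the independence figure is 1 − 0.95⁴ = 18.5%. The last-but-one column is to be read against that, not against 14.3%.

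**Step 4. Two ways to restore 5%.** (a) One confirmatory comparison, prevalence at one fixed cut-off: alpha stays 0.05 and 475 per group stands. (b) Three co-equal comparisons with a Bonferroni split, 0.05 / 3 = 0.0167: the prevalence comparison needs 616 per group with continuity correction (588 without), and 616 / 0.95 = 649 per group, or 1,298 in total. At 475 per group, power for 20% against 13% falls from 82.9% to 69.7% (pooled formula, no correction). Option (b) is shown only to compare costs; the article does not propose it.

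**The case against.** The best reply is that the sample size already points to prevalence. The whole trial is sized on it, the number reproduces, and the only 5% in the article belongs to that test. A reader might infer from the list of three comparisons that the stated 5% is false or the sample size wrong. Neither follows. Each test keeps its level if fully specified in advance, and the sizing arithmetic is sound. Nor does the article say that one significant result of three is enough; the three simply will be compared. All this stands, and it limits the point to the primary conclusion.

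A reader might also count every analysis mentioned as a rival test. The text does not support that. Analysis of covariance is described as estimation, and the Discussion explains the adjusted analyses as handling day length at outcome measurement. The two cut-offs are cited as validation data, not offered as two trial definitions, and they affect prevalence only, not the median or the mean change.

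Finally, it may be said that an analysis plan not shown will settle this. Modelling detail can be left there. But the article has a section for the primary outcome, and that section sets out three comparisons without a lead. Sizing on prevalence suggests the intention without stating it, and even that intention leaves the cut-off open.

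**Conclusion.** The point holds in limited form. The primary outcome section names no deciding comparison, and the article adopts no cut-off for the comparison on which the trial was sized. If any of the three may be claimed, the false-positive chance for the primary conclusion is about 11% to 13%, and about 13% to 16% if the cut-off is also open. Leaving the cut-off open takes the prevalence test alone to about 8% to 9%.

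The 14.3% figure needs no assumption about scores. The simulated ranges rest on an assumed GDS-15 distribution, but every setting tried at least doubled 5%. The documents give no basis for quantifying how power changes between the two cut-offs, because the one behind the 20.0% is not stated.

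**What to change.** In Primary outcome, name one confirmatory comparison: prevalence of depression at the 3-month outcome visit, as that visit is defined for each group in Methods/Design, at the single GDS-15 cut-off that produced the 20.0% (101/506) in Sample size. State that cut-off in both sections. In Statistical analysis, name one test for this comparison, either the chi-square test or the logistic regression with its covariates listed, and label the other supportive.

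Make median score and mean change secondary. The score is preferably analysed by ANCOVA with baseline GDS-15, together with the day-length adjustment promised in the Abstract and Discussion. Making the score the primary instead would detach it from the sample size, since the article gives no SD or target difference for it.

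Cost: wording in the protocol and the registry entry, and confirmation of the cohort's cut-off. Trial status says that recruitment had not begun. The 475 per group and 1,000 in total are unchanged.

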### Secondary outcomes

As secondary outcomes, we will measure subjective and actigraph-measured sleep quality, sleepiness, glycated haemoglobin (HbA1c), fasting plasma glucose (FPG), triglyceride (TG), low-density lipoprotein cholesterol (LDL-C), high-density lipoprotein cholesterol (HDL-C), body mass index (BMI), abdominal circumference, circadian rhythm of physical activity and wrist skin temperature, urinary melatonin metabolite, chronotype, post-illumination pupil response (PIPR), visual acuity, and subjective visual function.

### Self-reported questionnaires

Depressive symptoms are measured using GDS-15; a self-administered questionnaire consisting of 15 items
[43]. The sensitivity and specificity of GDS-15 compared with diagnosis according to the Diagnostic and Statistical Manual of Mental Disorders (fourth edition) was 92.7% and 54.8% with a cut-off point of four out of five, and 84.8% and 67.7% with a cut-off point of six out of seven, respectively
[44]. According to a meta-analysis about the validity of GDS-15, the mean sensitivity was 0.805 and the mean specificity was 0.750, respectively
[45]. A higher score on the GDS-15 was significantly associated with self-report and clinician-administered measures of suicidal ideation
[46] and higher rates of suicide
[47]. Subjective sleep quality and daytime sleepiness are assessed using the Pittsburgh Sleep Quality Index (PSQI)
[48] and the Epworth Sleepiness Scale (ESS)
[49, 50], respectively. Chronotype and subjective visual function are determined by the ‘morningness-eveningness’ questionnaire (MEQ)
[51], the Munich Chronotype Questionnaire (MCTQ)
[52], and the National Eye Institute Visual Function Questionnaire (NEI VFQ25)
[53, 54].

### Analysis of venous blood sample

Overnight fasting venous blood samples will be analysed at a commercial laboratory (SRL Co. Inc., Tokyo, Japan) using standard clinical chemistry analysis to determine the concentrations of HbA1c, FPG, TG, LDL-C, and HDL-C.

### Morning spot urine

We will measure 6-sulfatoxymelatonin (aMT6-s) in a morning spot urine sample. Peak nocturnal plasma melatonin is significantly associated with aMT6-s in subsequent morning spot urine (r = 0.69)
[55, 56]. Urinary aMT6-s concentration will be measured at a commercial laboratory (SRL Co. Inc. Tokyo, Japan) using an ELISA kit (RE54031; IBL International, Hamburg, Germany).

### Actigraph

Objective sleep will be measured by an actigraph (ActiSleep-BT Monitor; ActiGraph Inc., Florida, United States), worn on the non-dominant arm for five days, including weekdays and a weekend. Participants will be instructed to keep a standardised sleep diary logging bed time and rising time. Sleep parameters such as total sleep time, sleep efficiency, sleep onset latency, and wake after sleep onset will be calculated with ActiLife 6 (ActiGraph Inc. Florida, USA). A validation study of this device showed moderate to high agreement with sleep parameters as measured by polysomnography
[57].

### Circadian rhythm of physical activity and wrist skin temperature

Invasively measured biomarkers usually used in laboratory settings, such as fluctuation of plasma cortisol, melatonin, and rectal temperature, are difficult to conduct because they disturb the normal life of participants. To assess the influence of cataract surgery on internal biological rhythms using non-invasive methods, we will measure the phase and amplitude of circadian activity rhythm and the wrist skin temperature.

According to large-scale prospective cohort studies, decreased amplitude, later phase, and decreased robustness of circadian activity rhythm showed a significantly higher hazard ratio for incidents of cognitive disorders, cancer mortality, and all-cause mortality
[58–60]. Wrist temperature reveals heat loss from arteriovenous anastomoses at the skin
[61], and shows a mirror image of core body temperature
[62] and blood pressure
[63, 64]. The validity of using wrist skin temperature as an acceptable measure to assess circadian phase is indicated by the significant correlation of dim light melatonin onset and the increase of wrist skin temperature in the evening in real-life situations (r = 0.76)
[65]. The wrist skin temperature at inside of the wrist, near the radial artery of the dominant arm, will be measured using a temperature data logger (Thermochron iButton; Maxim/Dallas, Dallas, Texas, United States) at three-minute intervals
[62].

### Post-illumination pupil response

By pharmacological blockage of the rod and cone cells, the melanopsin-associated ganglion cell response is isolated as a slow, maintained depolarisation to light stimulation, which repolarises slowly after light-offset *in vitro*
[66]. This PIPR is indicated as an index of the sensitivity of the melanopsin-containing ipRGC pathway
[67]. In the present study, baseline and sustained pupil diameter after blue and red light stimulation will be measured. Baseline pupil diameter is the average pupil diameter in a seven-second period before light onset. Sustained pupil diameter is the average from 10 to 40 seconds after light offset. PIPR (mm), PIPR change (%), net PIPR (mm), and net PIPR change (%) will be calculated as follows
[68]:

### Other variables

Using a standardised questionnaire, trained researchers will interview participants about basic characteristics, such as age, gender, smoking and drinking habits, past history of cardiovascular events, stroke, cancer, medication, household income, years of education, and history of shift work. BMI will be calculated as weight per height (kg/m^2^). Waist circumference will be measured at the level of the umbilicus, in the standing position.

### Sample size

According to the HEIJO-KYO study
[26], a community-based cohort study among the elderly (mean age ± standard deviation: 72 ± 7.1) in the same district as the present study, the prevalence of depression was 20.0% (101 out of 506)
[37]. To detect its 7% difference as significant at a two-sided α level of 5% with a power of 80%, it was calculated that 475 participants in each group would be required. Assuming a dropout of 5%, we estimated that a total of 1,000 participants would be needed.

### Randomization and masking

Allocation concealment will be maintained by central randomization using computer-generated random sequences, independent of care-providers. The results of the allocation will be masked from the assessors of the outcomes, but will be available to both the care providers and the participants.

### Statistical analysis

We will compare the outcomes between the control group and the intervention group based on the intention-to-treat principle. For missing values due to loss to follow-up after baseline measurement, we will impute baseline data using the last observation carried forward (LOCF) method. For continuous variables with normal distributions, the mean and standard deviation will be reported. For variables not distributed normally, the median and interquartile range will be reported. Means, medians, and proportions will be compared using the t test, the Mann-Whitney U test, and the χ^2^ test, respectively. We will use analysis of covariance to estimate adjusted mean values and 95% CIs. The prevalence of the two groups will be tested using multivariate logistic regression analysis. To assess the phase, amplitude, and robustness of the circadian rhythm, we will use the cosinor model
[69], the sigmoidally transformed cosine model
[70], and the generalised additive model
[71]. We will conduct a subgroup analysis at baseline according to the severity of cataract and chronotype.

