## Methods/Design

All intervention processes associated with the present study are conducted at Nara Medical University hospital. The protocol of this study has been registered at the University Hospital Medical Information Network Clinical Trials Registry (UMIN-CTR, identifier: UMIN000014559). The CLOCK-IOL (Cataract Surgery and Circadian Biological Rhythm among Japanese Older People with Cataract in Nara, Kansai Region: Influence of Intra Ocular Lens Implantation) study was approved by the institutional review board of Nara Medical University (approval number: 13-032). This research complies with the Declaration of Helsinki. Before enrolment to this study, we will obtain written informed consent from all participants.

We will include participants continuously through the year with similar speed, and inclusion of the present study will finish at the same date as the started year. After baseline measurements, all participants will be randomly allocated to either the intervention group or the control group in a 1:1 ratio without restrictions such as blocking and stratification. The outcomes among the intervention group will be measured at three months after surgery. Among the control group, the outcomes will be measured at three months after baseline. The control group will receive delayed cataract surgery shortly after the outcome measurement (Figure 
1).

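### With a single outcome visit, LOCF gives every lost participant a zero change; at the planned 5% loss this costs about 2 points of power and roughly cancels the dropout allowance

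*Protocol article*

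**What the plan says.** The missing-data rule is in the Statistical analysis section of the protocol article: "For missing values due to loss to follow-up after baseline measurement, we will impute baseline data using the last observation carried forward (LOCF) method". It sits inside an intention-to-treat comparison: "We will compare the outcomes between the control group and the intervention group based on the intention-to-treat principle".

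Methods/Design gives one outcome assessment per arm. For surgery: "The outcomes among the intervention group will be measured at three months after surgery". For control: "Among the control group, the outcomes will be measured at three months after baseline". No intermediate visit is described, so the last observation before a missed outcome visit is the baseline one.

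The primary outcome, GDS-15, is compared as prevalence of depression, as a median and as a change: "the mean value of difference between baseline and three months later will be compared between the intervention group and the control group".

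The Sample size section starts from a prevalence of 20.0% in a local cohort, aims "To detect its 7% difference as significant" at two-sided 5% and 80% power, and arrives at 475 per group. It then adds an allowance: "Assuming a dropout of 5%, we estimated that a total of 1,000 participants would be needed".

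**The concern.** LOCF is usually discussed for trials with several visits, where the carried value at least comes from some way into follow-up. Here it can only be the value from before randomisation, which has three consequences.

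- For the change in GDS-15, each lost participant contributes exactly zero, whatever happened to them.
- A participant lost after surgery enters the comparison with pre-operative values. This applies to every outcome, including visual acuity, for which the Discussion itself calls the benefit of surgery established.
- The imputed values go into the t test, Mann-Whitney, χ², ANCOVA and logistic analyses as ordinary data, so the standard errors carry no uncertainty for the missing outcomes.

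The sample size and the analysis also treat dropouts differently. The extra 50 participants are added as though lost patients leave the analysis. The LOCF rule instead keeps them in it, with no effect. At stake are the size of the estimated effect, part of the planned power and, if loss is unequal, the direction of the bias.

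**Working it through.** **Inputs.** From the Sample size section: prevalence 20%, a 7-point difference (read as 20% against 13%), two-sided α 5%, power 80%, 475 per group, 5% dropout, 1,000 in total. From Methods/Design: 1:1 allocation, one outcome visit per arm. Loss above 5%, and any difference in loss between arms, are assumptions.

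**Step 1: the plan's own figure.** With p₁ = 0.20, p₂ = 0.13 and mean 0.165:

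n = [1.960·√(2·0.165·0.835) + 0.842·√(0.20·0.80 + 0.13·0.87)]² / 0.07² = 440.2, so 441 per group.

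With continuity correction, (n/4)·[1 + √(1 + 4/(n·0.07))]² = 468.3, so 469. That is within about 1% of the stated 475; the uncorrected 441 is not close. Reading the difference as a rise to 27% gives 575, or 603 with correction, which fits worse. The allowance is exact: 475/0.95 = 500 per group.

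**Step 2: what the rule does to the difference.** Assume loss d in both arms, 20% prevalence among controls and in dropouts' baseline values, and 13% after surgery for everyone, including dropouts had they been seen. The surgery arm then shows 13(1 − d) + 20d percent, and the difference is 7(1 − d). At d = 0.05 the surgery arm shows 13.35% and the difference is 6.65 points.

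**Step 3: power at 500 randomised per arm.** Power = Φ{[Δ√n − 1.960·√(2p̄(1 − p̄))] / √(p₁(1 − p₁) + p₂(1 − p₂))}. For LOCF at d = 0.05 (Δ = 0.0665, n = 500): (1.487 − 1.033)/0.525 = 0.864, which gives 80.6%. The corrected figures use the n that the continuity correction would inflate to the available number. Observed-outcome figures use 500(1− d) per arm and the full 7 points.

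| Loss, both arms | LOCF difference | LOCF power, corrected / uncorrected | Observed outcomes, corrected / uncorrected |
|---|---|---|---|
| 5% (planned) | 6.65 | 78.2% / 80.6% | 80.6% / 82.9% |
| 10% (assumed) | 6.30 | 73.2% / 75.9% | 78.3% / 80.9% |
| 20% (assumed) | 5.60 | 61.9% / 65.1% | 73.1% / 76.1% |

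**Step 4: the allowance.** With no allowance, 475 randomised and 5% lost leave 475 × 0.95 = 451 observed per arm, with power 78.4% corrected and 81.0% uncorrected. LOCF on 500 gives 78.2% and 80.6%. So the 25 extra participants per arm buy about what the rule takes away. Keeping 80% power under LOCF at 5% loss needs 522 per arm (corrected).

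**Step 5: unequal loss.** Let the true mean changes be δₛ (surgery) and δ꜀ (control), and the loss rates dₛ and d꜀. LOCF estimates (1 − dₛ)δₛ − (1 − d꜀)δ꜀ = (1 − dₛ)(δₛ − δ꜀) + (d꜀ − dₛ)δ꜀. The first term is attenuation. The second can have either sign and is zero only if loss is equal or controls do not change.

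On the prevalence scale, assume no true effect, 8% loss in the surgery arm and 2% in control.
- If both arms fall from 20% to 13%, LOCF shows 0.92·13 + 0.08·20 = 13.56% against 0.98·13 + 0.02·20 = 13.14%, a false 0.42 points against surgery.
- If both arms rise to 27%, it shows 26.44% against 26.86%, a false 0.42 points in favour of surgery.

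**Step 6: standard error.** In a simulated ANCOVA (assumed baseline-outcome correlation 0.6, true effect −0.20 SD, 5% loss in each arm), LOCF gave −0.191 with standard error 0.050. Observed cases gave −0.201 with 0.052. With no true effect, the rejection rates were 5.2% and 5.1%.

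**The case against.** The strongest reply is that the damage is small where the article's own figures apply. The only loss rate it gives is 5%. There the shift is 0.35 points, the uncorrected power of 80.6% stays above target, and even the corrected figure falls only to 78.2%. That stands. The 10% and 20% rows are a range, not a forecast.

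Several stronger readings are tempting but not supported:

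- **That LOCF always pulls the effect to zero.** This follows under the assumptions of step 2. Under unequal loss with drift, the bias can run either way. For the same reason, the rule cannot be defended as reliably conservative.
- **That it produces false positives.** A simulation with 15% loss against 5%, a common drift of 0.5 SD and no true effect rejected in about 17% of trials. Neither input is in the article. The Discussion states a longer interval in the surgery arm and a possible seasonal effect, but gives no arm-specific loss. With equal loss, estimate and standard error shrink almost together and the error rate stays near 5%.
- **That all lost surgery-arm patients get wrong values.** Some may be lost before their operation, and for them the pre-operative value is not plainly wrong. The clearest case, visual acuity, is a secondary outcome. For GDS-15 the benefit is the hypothesis under test.
- **That the lack of a sensitivity analysis is an error.** A condensed article may leave that to the full protocol or analysis plan. The finding is the rule that is stated.

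It is also fair to say that a model on observed outcomes needs its own untestable assumption. That assumption should be written down.

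**Conclusion.** The concern holds, at modest size. The article commits to a rule that, with one visit per arm, sets every lost participant's change to zero and treats the result as data; nothing elsewhere in the article changes this. At the planned 5% loss the cost is 0.35 of the 7 points and about 2 points of power (2.4 with continuity correction, 2.3 without), which roughly cancels the dropout allowance. These figures assume equal loss, 20% prevalence in controls and dropouts, and full benefit in dropouts had they been observed. The cost grows with loss. The direction of bias is not assured if loss differs by arm and outcomes change with time or season. The plan should be changed, but this does not by itself invalidate the design.

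**What to change.** Replace LOCF as the primary rule with one of the following, under a stated assumption that outcomes are missing at random given the covariates used:

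- the baseline-adjusted model (ANCOVA for continuous outcomes, logistic regression for prevalence) fitted to all observed outcomes; or
- multiple imputation by arm, using baseline score, age, cataract grade and season.

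Add a delta-shift sensitivity analysis that moves the missing outcomes away from that assumption, separately by arm. Keep baseline carried forward at most as a further sensitivity analysis. A jump-to-control analysis would add little: with controls constant at 20% it gives the surgery arm 13(1 − d) + 20d percent, the same value as LOCF.

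The cost is a change of wording and some extra programming, with no new data. The Trial status section says recruitment had not begun, so the change could be made before any outcome is seen. The remaining downside is that missing at random cannot be tested; the delta-shift analysis shows how far the conclusion depends on it.
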